#### Procedures for missing data

Some service users may leave the study early, but we plan to follow up as many as possible. We plan to carry out a sensitivity analysis and a selection model to test whether data missing is at random and whether the leaving early has an effect on treatment effects. To see if the data is missing at random, we will analyse whether it correlates to or is associated with the rest of the data. For data missing at random, a multiple imputation method will be used to fill missing values. If data missing is not at random or it may bias treatment effects, we shall run a selection-bias correction model (mixture model) to adjust for such bias.

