Assuming that 5% of the service users who receive standard care visit a dentist, to then detect a 15% increase in the proportion of those who visit a dentist in the dental intervention arm with 80% power at 0.05 significance level, we need 176 service users for a single-centre trial, after adjusting for the cluster effect by multiplying this by the design effect, we need to recruit 334 service users. After further adjusting for 20% of service users lost to follow up, the final number of service users we need to recruit is 418. Other situations with various proportions of visits to a dentist in standard care are also presented in Table 1.

All these assumptions we have made in this power calculation may be correct or all may be incorrect. It is, at this point, quite impossible to say. As can be seen from the background, no studies have been undertaken in this area. There is no data to even guess what any effect may or may not be. This is a pioneering trial that will set a standard and will allow researchers in the future to have some benchmark off which to work.

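### The missing-data rule chooses between multiple imputation and a bias-correction model using a check that cannot tell missing at random from missing not at random

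*Protocol article*

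**What the plan says.** All of the relevant text is in the protocol article, under Procedures for missing data. Four statements matter.

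- Purpose of the extra models: "We plan to carry out a sensitivity analysis and a selection model to test whether data missing is at random", and also to see whether early leaving affects the treatment effect.
- The check, for deciding whether missing data are missing at random: "we will analyse whether it correlates to or is associated with the rest of the data".
- First branch: "For data missing at random, a multiple imputation method will be used to fill missing values".
- Second branch: "If data missing is not at random or it may bias treatment effects, we shall run a selection-bias correction model (mixture model) to adjust for" that bias.

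The section does not say which result of the check counts as missing at random. It gives no criterion for deciding that missingness may bias the treatment effect. It names no missing-data analysis that would be primary whatever the check shows. The Data analysis section separately expects multilevel modelling or random effects methods for the main comparison.

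**The concern.** The check looks only at observed data. The question it is meant to answer, MAR or MNAR, is about how missingness relates to the outcome values that were not observed. A rule that links the two can misdirect the analysis, and it can lend an untested assumption the appearance of having been confirmed.

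This matters because the primary outcome is a dental visit reported on the checklist. A care co-ordinator has to complete that checklist, and the service user may decline to answer it. Users also leave the trial if their co-ordinator or team withdraws consent. People who disengage from the service could plausibly be both less likely to visit a dentist and less likely to have an outcome recorded. That is the MNAR situation which the check cannot see.

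**Working it through.** **Inputs.** From Sample size and the first row of Table 1: 5% visiting under standard care, 20% under the intervention, 20% lost to follow-up. From Procedures for missing data: the check and the two branches. The missingness mechanisms in step 3 are assumptions made for illustration; the documents give none.

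**Step 1. The plan's own figures.** The missing-data section states no number. The figures borrowed from the sample-size section do reproduce. A two-sided 5% test with 80% power and a continuity correction gives 176 in total for 5% v 20%. Then 176 × 1.9 = 334.4, given as 334, and 334 / 0.8 = 417.5, given as 418. Nothing in this point changes them.

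**Step 2. What the check can identify.** Let R mark a missing outcome, Y the outcome and X the observed data.

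- Missing completely at random (MCAR): P(R | X, Y) = P(R).
- MAR: P(R | X, Y) = P(R | X).
- MNAR: P(R | X, Y) still depends on Y after conditioning on X.

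The check estimates P(R | X). If that varies with X, MCAR is rejected. Both MAR and MNAR are compatible with P(R | X) varying or being flat, so the result does not choose between them. The two possible readings of the rule are:

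| Association found is taken to mean | What can go wrong |
|---|---|
| Not at random | MAR data, for which imputation using X is valid, are sent away from imputation |
| At random | MNAR data that also correlate with X are imputed as if MAR had been verified |

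The selection model named as a further test does not close the gap. It separates MAR from MNAR only through distributional or exclusion assumptions that the data cannot check.

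**Step 3. Illustration by simulation.** There were 418 users, 2,000 replicates, clustering ignored, about 20% missing, and true rates of 5% v 20% (15.0 points). The check was a logistic test, at the 5% level, of missingness on arm and one observed binary covariate. The estimate was a MAR-based one, standardised on that covariate.

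| Assumed mechanism | Check significant | MAR-based difference |
|---|---|---|
| MCAR, 20% | 4% of runs | 15.1 points |
| MAR, 10% v 30% by covariate | 99.8% of runs | 15.0 points |
| MNAR, 5% of visitors and 22% of non-visitors missing, covariate unrelated to outcome | 8% of runs | 17.2 points |

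The MNAR row can be confirmed by hand.

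- Intervention: 0.20 × 0.95 / (0.20 × 0.95 + 0.80 × 0.78) = 0.190 / 0.814 = 23.3%.
- Control: 0.05 × 0.95 / (0.05 × 0.95 + 0.95 × 0.78) = 0.0475 / 0.7885 = 6.0%.
- Difference: 17.3 points, against 17.2 simulated.

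The check fires where the MAR-based estimate is sound and is mostly silent where it is biased. The size of the bias belongs to the assumed mechanism. The inability to discriminate does not.

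**Step 4. What MNAR could do at the planned loss.** With a fraction m missing, an arm's rate is (1 − m) × observed rate + m × rate among leavers. Put m = 0.2 and observed rates of 20% and 5%.

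- Only intervention leavers never visit, and control leavers visit at the observed rate: 0.8 × 20 + 0.2 × 0 = 16, so 16 − 5 = 11 points.
- Leavers in both arms never visit: 16 − (0.8 × 5 + 0.2 × 0) = 16 − 4 = 12 points.

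**The case against.** The best defence is that the section is loosely worded rather than committed to a bad procedure. Several parts of that defence stand.

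- **Sensitivity work is planned.** A reader might infer that the plan makes no provision for departures from MAR. The text does commit to a sensitivity analysis. Detail such as delta ranges may sit in an analysis plan that is not shown. What can be criticised is its stated use, which is to test the mechanism.
- **The headline estimate.** A reader might infer that the check decides which result becomes the trial's main finding. The article does not say so. It sets no threshold, does not say that the second model replaces the first, and describes the main analysis elsewhere.
- **Direction of the rule.** The text does not say that an association means not at random. The opposite reading is available, and on it, using imputation when missingness is explained by observed data is a reasonable sequence. It still cannot show that MAR holds.
- **Terminology.** The second branch might be taken to confuse selection models with mixture models. It can also be read as a mixture model used to correct selection bias, so no separate error is claimed.
- **Size.** If every leaver's outcome is set to the worst and the best case, the difference runs from (0.8 × 20) − (0.8 × 5 + 20) = −8 to (0.8 × 20 + 20) − (0.8 × 5) = +32 points. A reader might take that range as the harm done by this rule. It is the bound for 20% loss at these rates under any missing-data plan, and a better plan would not narrow it.

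None of this rescues the rule. The protocol states how MAR will be judged and links a method to each answer, so this is not a detail left for later. The trigger based on possible bias cannot be judged from observed data either.

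**Conclusion.** The point holds in a limited form. As written, the rule uses an association between missingness and observed data to decide whether data are MAR, and assigns the method accordingly. That association speaks only against MCAR, so under either reading the rule can send data to the wrong method. This follows from the definitions and needs no assumption about the trial, so confidence is high.

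The consequence for the estimate cannot be fixed from the documents. The falls from 15 to 11 or 12 points assume 20% loss in each arm, observed rates of 5% and 20% (one of seven scenarios in Table 1), and leavers who never visit in the arms named. They show what an unexamined MNAR mechanism could do and are not a forecast. The plan should be corrected, but the defect does not undermine the design or the sample size.

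**What to change.** - Delete the rule that lets the check choose the method.
- Prespecify one primary analysis under a stated MAR assumption that respects team clustering: either the multilevel model already expected, or multiple imputation compatible with it. Keep it simple. With about five teams per arm, imputing separately by arm with team as a level plus county and caseload size would ask too much of the data. The demographics listed under Procedure are team-level, and control teams are not asked to use the checklist until a year later. Few individual-level auxiliaries are therefore evident in that arm, and imputation may add little to the multilevel model.
- Use observed associations with missingness only to choose auxiliary variables.
- Redirect the sensitivity analysis already mentioned from testing the mechanism to measuring its effect. Report it always, whatever the check shows. One suitable form is a delta-adjusted pattern-mixture analysis with deltas allowed to differ by arm, taken to the point where the conclusion changes.

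The cost is revised wording and a little extra computation. The change should be made before outcome data are examined, so that the choice of method cannot follow the results.

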#### Data monitoring

Monitoring of trial data includes confirmation of informed consent, source data verification, data storage and data transfer procedures, local quality control checks and procedures, back-up and disaster recovery of any local databases and validation of data manipulation. Entries on Case Report Forms (CRFs) will be verified by inspection against the source data. A sample of CRFs (10% or as per the study risk assessment) will be checked on a regular basis for verification of all entries made. In addition, the subsequent capture of the data on the trial database will be checked. Where corrections are required, these will carry a full audit trail and justification as to why amendments were made.

Trial data and evidence of monitoring and systems audits will be made available for inspection by the REC as required. In keeping with the GCP guidelines and in accordance with the University of Nottingham’s Research Code of Conduct, the chief investigator will maintain all records and documents regarding the conduct of the study, which will be kept for at least seven years or for longer if required. If the responsible investigator is no longer able to maintain the study records, a second person will be nominated to take over this responsibility. The trial master file and trial documents held by the chief investigator on behalf of the sponsor shall be finally archived at secure archive facilities at the University of Nottingham. This archive shall include all trial databases and associated meta-data encryption codes.

#### Governance

The Advisory Group is a multidisciplinary group to give advice and direction to the overall project and will meet every six weeks to begin with but will also provide continuing support and meet every few months for the duration of the trial. The Steering Group will meet twice a year to monitor the overall progress of the trial, adherence to the protocol and patient safety. The Data Monitoring Group will meet once a year to assess the progress and safety of the trial while providing the sponsor with recommendations regarding trial modification, continuation or termination. The Management Group consists of the trial team and will meet every week regarding the day-to-day running of the trial and data collection. This group will also communicate any unexpected events to both the Steering Group and the Advisory Group.

## Trial status

Recruitment started in February 2012. As of August 2012, 10 EIP teams caring for a total of 1,074 service users have been randomised. Recruitment for new trial sites is underway.
